## Abstract

Perinatal depression disproportionally affects underserved communities, who need effective and accessible prevention programs. Reach Out, Stay strong, Essentials for new mothers (ROSE) has demonstrated effectiveness in preventing postpartum depression in underserved populations when delivered in person. This ongoing randomized controlled trial (RCT) tests the novel virtual implementation of ROSE as universal prevention in a Federally Qualified Health Center setting. We adopted the name, La Luz, for ROSE to be culturally relevant to our population. Pregnant individuals <30 gestational weeks (target *N* = 900) are randomized to either the virtual or in-person La Luz program, which consists of four 90-min group sessions. Groups are offered in English and Spanish, based on participants’ preference. Participants complete surveys at seven timepoints: before program, 28 gestational weeks, 35 gestational weeks, and 6-weeks, 3-months, 6-months, and 12-months postpartum. Primary outcomes are postpartum depression severity measured by the 20-item Symptom Checklist (SCL-20) and 10-item Center of Epidemiologic Studies Depression Scale (CESD-10). We will perform intent-to-treat analysis to test whether virtual La Luz is non-inferior to in-person La Luz. This study also evaluates implementation process and outcomes of both modalities of La Luz to inform the development of an implementation toolkit. This RCT contributes to our knowledge of perinatal depression prevention and addresses access barriers for underserved populations. If effectiveness of virtual La Luz is demonstrated, the new evidence for a scalable low-cost prevention can be used to reduce perinatal depression and offer accessible treatment options for people who face significant barriers to care. Clinicaltrials.gov registration identifier: NCT05766475.

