##### Primary outcomes.

Depression symptoms are measured using (1) the 20-item Symptom Checklist (SCL-20) developed from the full Symptom Checklist-90-R [59], and (2) the 10-item Center of Epidemiologic Studies Depression Scale (CESD-10) shortened based on the original 20-item scale [60,61]. Both SCL-20 and CESD-10 are reliable and valid measures of depressive symptom severity, including with pregnancy participants [7,21,22,62]. For both scales, participants provided ratings using a 4-point scale on their symptoms for the past week (CESD-10) or month (SCL-20). Item scores for each scale are summed to generate a total score, with higher scores indicating higher depression severity. The SCL-20 and CESD-10 scores will be analyzed dimensionally as the primary outcomes of this RCT.

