#### Analysis testing inferiority of virtual vs. in-person La Luz

3.6.1.

Primary analyses will use intent-to-treat design to evaluate the effectiveness of the intervention among all enrolled participants [66]. To test whether virtual La Luz will yield a similar benefit (i.e., is non-inferior) as in-person La Luz for perinatal depression, multilevel models (timepoints nested within participants) including random intercepts and slopes will be used. Multilevel modeling accounts for nested data structure and is robust to missing data [67]. In line with non-inferiority testing, we will use a one-sided test and statistical significance set at *p* < .05 with margin of non-inferiority set to an effect size Cohen’s *d* of 0.25 for our estimate contrasts of total change in our multilevel model. Model-based total change estimate will provide us flexibility if the change over time is nonlinear (i.e., log-linear, parabolic, piecewise, etc.). A negative effect size would indicate more reduction for virtual compared to in-person, whereas, a positive effect size would indicate more reduction for in-person compared to virtual. Non-inferiority will be shown if the effect size for contrast of total change yields a one-sided 95 % upper bound smaller than *d* = +0.25. If the one-sided 95 % upper bound is bigger than *d* = +0.25, the confidence interval for the true effect size of the contrast of total change does not lie totally within the non-inferior region, and non-inferiority cannot be concluded (illustrated in Fig. 2 with ±*d* as the indicated margins). Given that intent-to-treat approaches can bias non-inferiority trials toward finding the interventions to be non-inferior, we will also conduct a sensitivity analysis including only participants who complete the intervention [68,69]. Secondary analyses will follow the same analytic procedures but with EPDS scores collected from electronic health records as the outcome.

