## Figures and Tables

**Fig. 1. F1:**
[figure not shown]
Overview of study flow. Note. This figure provides an overview of study procedures, including randomization, intervention, and timing of assessments. ROSE = Reach Out, Stay strong, Essentials for new mothers program. * If a participant is enrolled at 28 or 29 gestational weeks, they will receive their 28-gestational week survey 1–2 days after their baseline survey.

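### Non-inferiority rests on a total change with unnamed endpoints and an open time curve, while the abstract names postpartum severity as primary

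*Protocol article*

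**What the plan says.** The abstract of the protocol article states: "Primary outcomes are postpartum depression severity measured by the 20-item Symptom Checklist (SCL-20", followed by the CESD-10. The primary-outcome paragraph of section 3.5.2 gives no timepoint: "The SCL-20 and CESD-10 scores will be analyzed dimensionally as the primary outcomes of this RCT". The first aim (section 2) and section 3.6.1 refer to perinatal depression, which the introduction defines as running from pregnancy to one year after birth.

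Section 3.6.1 sets the model: "multilevel models (timepoints nested within participants) including random intercepts and slopes will be used". The decision rule is: "Non-inferiority will be shown if the effect size for contrast of total change yields a one-sided 95 % upper bound smaller than" d = +0.25. On the shape of change over time it adds: "Model-based total change estimate will provide us flexibility if the change over time is nonlinear (i.e., log-linear, parabolic, piecewise, etc". No start or end visit for total change is given. Section 3.5.1 lists seven assessments: baseline, 28 and 35 gestational weeks, and 6 weeks, 3, 6 and 12 months postpartum.

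**The concern.** The trial's conclusion is one bound set against one margin, so the quantity being bounded has to be fixed. Here it is fixed neither by its endpoints nor by its shape. A linear, quadratic, piecewise or logarithmic curve fitted to the same seven means gives a different fitted change from first to last visit. If the arms separate soon after the groups and stay apart, a smooth curve cannot follow the step. It raises the fitted difference at baseline or lowers it at the end, so the contrast is too small. In a non-inferiority trial that error favours a false pass.

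The outcome named in the abstract is also not the quantity tested. Change from baseline to the last visit can be near zero although the arms differed through the first months after birth.

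**Working it through.** **Inputs from the protocol article.** 900 participants and 20% attrition (section 3.1.1); margin d = 0.25 and one-sided p < .05 (section 3.6.1); seven visits (section 3.5.1); enrolment before 30 gestational weeks.

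**Assumed, because not stated.** 1:1 allocation, so 900 × 0.8 / 2 = 360 per arm. Baseline at 12, 18 or 24 weeks in turn, with birth at week 40. Baseline SD 1, random-intercept variance (ICC) 0.4 or 0.6, residual variance 1 − ICC. Random-slope variance 0.15 with time scaled 0 to 1. Complete data, known covariance, no clustering by group. Total change is read as baseline to 12 months.

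**The plan's own figure.** Power is not stated, so 900 cannot be strictly reproduced. For a single endpoint with SD 1, the standard error is √(2/360) = 0.0745 and power is Φ(0.25/0.0745 − 1.645) = Φ(1.71) = 95.6%. The target of 900 is consistent with about 95% power and is not in question.

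**Method.** Let δ be the true arm differences at the seven visits. Their estimates have covariance D = (2/360)·[Z·diag(ICC, 0.15)·Z′ + (1 − ICC)·I]. Each curve gives a design matrix X. With c the curve at 12 months minus the curve at baseline, the generalised least-squares weights are w = c′(X′D⁻¹X)⁻¹X′D⁻¹. The expected contrast is w·δ and SE = √(w·D·w′). The chance of declaring non-inferiority is Φ((0.25 − 1.645·SE − w·δ)/SE). The log curve uses log(1 + weeks since baseline); the piecewise curve has its knot at birth.

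**Case 1: virtual worse by 0.25 at every visit after baseline.** One setting in full (baseline at 18 weeks, ICC 0.6, baseline free by arm):

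| Time form | Expected contrast | SE | Pass limit (0.25 − 1.645·SE) | Declared non-inferior |
|---|---|---|---|---|
| Linear | 0.149 | 0.0638 | 0.145 | 47% |
| Quadratic | 0.150 | 0.0638 | 0.145 | 47% |
| Piecewise | 0.182 | 0.0645 | 0.144 | 28% |
| Log | 0.268 | 0.0626 | 0.147 | 3% |
| Visit as category | 0.250 | 0.0726 | 0.131 | 5% |

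The last row can be checked by hand: variance 2(1 − 0.6) + 0.15 = 0.95; SE √(2 × 0.95/360) = 0.0726; (0.131 − 0.250)/0.0726 ≈ −1.645.

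Over all three baseline times and both ICCs:
- Baseline free by arm: 27–65% linear, 24–70% quadratic, 15–52% piecewise, 2–8% log, 5% categorical.
- Baseline constrained equal: about 4–38% linear, 17–56% quadratic, 11–38% piecewise, 1–3% log, 5% categorical.

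The shrinkage needs no correlation assumption. Unweighted fits to a constant 0.25 deficit with baseline at 20 weeks give 0.141 linear, 0.139 quadratic, 0.172 piecewise and 0.249 log.

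**Case 2: a deficit that fades.** Take 0.25 at 6 weeks and 3 months, 0.12 at 6 months, 0 at 12 months and 0 before birth. The mean postpartum deficit is (0.25 + 0.25 + 0.12 + 0)/4 = 0.155. Baseline-to-12-month change with categorical visits has expectation 0. It passes with probability Φ(0.25/0.0866 − 1.645) = 89% at ICC 0.4, where SE = √(2 × 1.35/360), and Φ(0.25/0.0726 − 1.645) = 96% at ICC 0.6 (baseline free by arm). A categorical time model alone therefore does not cure the problem; the contrast must be named too.

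**How often the curves disagree in the same data** (20,000 simulated trials per setting, four curves): 16–62% with the constant 0.25 deficit, 32–41% with a constant 0.15 deficit, 28–58% with the fading deficit, and 1–5% when the arms are equal.

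**The case against.** The strongest reply is that an article may leave curve selection to the full analysis plan, and that section 3.2 says staff are blind to condition during data analysis. A reader might infer that the curve will be picked to suit the result and that the error rate is uncontrolled for that reason. The text does not support this: it says neither when nor by whom the form is chosen. The point survives all the same. The section gives the model, margin and decision rule and presents the open form as an advantage, so this is more than silence. The shrinkage in Case 1 also arises with a curve chosen blind to arm.

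Second, the word postpartum attaches to the primary outcome only in the abstract; a contrast over the whole course fits the perinatal wording of the aim. That is fair. The passages need reconciling, and they do not prove that the analysis targets the wrong outcome.

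Third, the results depend on assumed trajectories. This stands: with equal arms the choice of curve hardly matters.

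Other inferences go too far. It is tempting to say that precision is thrown away, but the plan is a multilevel model over all visits, not a first-to-last change score, and baseline handling is not stated. The Fig. 1 note that some participants get "they will receive their 28-gestational week survey 1–2 days after their baseline survey" concerns only those enrolled at 28 or 29 weeks, whose share is not given. The unnamed SD behind d may be in the full plan and is not counted as a fault here.

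**Conclusion.** The point holds in this form: the decisive quantity is left open in endpoints and curve, and the article describes the primary outcome in two ways. Under a constant true deficit at the margin, linear, quadratic and piecewise curves declare non-inferiority in roughly 15–70% of trials with baseline free by arm, where 5% is intended; the log curve gives 2–8%. Constraining the baseline reduces the excess but does not remove it. A baseline-to-12-month change would also usually pass over a deficit that has faded by 12 months. These sizes rest on the assumed correlations, visit timing, complete data and arm differences, and show what can happen, not what will. The trial is not shown to be underpowered.

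**What to change.** Before unblinding, reconcile the abstract with section 3.6.1 by naming one primary contrast that matches the primary outcome. A suitable choice is the virtual minus in-person difference in mean score over the four postpartum visits; if the sponsor intends another period, that should be stated in both places. Estimate the contrast from a repeated-measures model with visit as a category, and either adjust for the baseline score or constrain baseline means to be equal. Keep the 28- and 35-week visits in the model but out of this contrast. Name the SD that defines d at the same time. Make growth-curve total change a secondary analysis.

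The cost is wording: the assessments are already scheduled and nothing new is collected. The growth-curve model loses its primary role, and the course during pregnancy has to be reported separately. Baseline adjustment should also improve precision, by an amount that depends on baseline handling the article does not state.

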The preventive intervention (i.e., ROSE) tested in this study addresses many of these barriers by adopting a universal prevention approach, delivering culturally sensitive treatment in English and Spanish, and testing telehealth delivery. Offering ROSE as a universal prevention within the obstetric setting can help improve access by normalizing and de-stigmatizing participation in prevention programs, especially for those who experience elevated social stigma and fear of negative consequences associated with being identified as needing interventions (e.g., racially and ethnically minoritized individuals) [40]. Additionally, providing services in patients’ preferred language can help reduce barriers to care and attrition by easing communication, acknowledging the patient’s language and cultural background, and facilitating bonding and sense of community among people with shared language backgrounds [30,41]. In particular, the Hispanic and Latine population is the largest, and one of the fastest-growing, racial and ethnic minoritized groups in the United States [42], and over 43 million people speak Spanish at home [43]. Additionally, the Hispanic and Latine population has one of the highest fertility rates across various racial and ethnic groups in the United States [44]. As such, providing perinatal prevention programs in Spanish when preferred can promote acceptability and adoption of these programs among Spanish-speaking pregnant individuals. However, although ROSE is available in Spanish [45], the effectiveness of ROSE in Spanish has not been empirically tested.

Expanding ROSE through virtual delivery offers another transformative strategy to improve access of care in underserved populations [46,47]. To date, trials establishing the efficacy of ROSE have only been conducted in person [23,24,27,28,48,49]. Given its widespread scalability, telehealth has the potential to enhance mental health service delivery by reducing access barriers, particularly among minoritized groups [46,47]. For example, prior research with ROSE found that Black individuals identified transportation as a major barrier [49]. Specific to perinatal depression treatment, telehealth can be an effective means of intervention [50,51]. Thus, a preventive intervention delivered via telehealth is a potentially scalable, sustainable, and effective delivery model in real-world settings.

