#### Study population and recruitment site

3.1.1.

We aim to recruit 900 pregnant individuals from Denver Health obstetrics clinics. Pregnant individuals (18 years or older) who are English or Spanish speaking and at less than 30 gestational weeks are eligible. Individuals at 30 or more gestational weeks are excluded due to insufficient time to complete ROSE prior to delivery. The target sample size was determined based on power analyses accounting for an estimated 20 % attrition rate (10 % during pregnancy and an additional 10 % postpartum) and our primary analyses testing inferiority of virtual to in-person La Luz (see below).

Denver Health is a Federally Qualified Health Center serving low resourced and underserved pregnant individuals. The obstetrics clinics at Denver Health serve individuals from the surrounding urban metropolitan Denver area. Denver is a racially and ethnically diverse city, which is reflected in the Denver Health patient population. Among all patients who received care from Denver Health in 2023, 49 % identify as Hispanic/Latine, 13 % Black or African American, 30 % non-Hispanic White, and 4 % Asian or Pacific Islander [54]. Spanish-speaking patients make up a substantial portion of the Denver Health patient population, and some patients speak only Spanish [55].

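### The one named check on the intent-to-treat verdict is an unadjusted completer comparison, which can err in either direction if selection into completion differs by modality

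*Protocol article*

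**What the plan says.** Section 3.6.1 of the protocol article bases the primary verdict on an intent-to-treat multilevel model. The test is one-sided at 5%, with "margin of non-inferiority set to an effect size Cohen’s *d* of 0.25" on the contrast of total change. The decision rule is "Non-inferiority will be shown if the effect size for contrast of total change yields a one-sided 95 % upper bound smaller than" d = +0.25. Positive values mean more reduction in person.

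The section then gives its reason for a second look, "Given that intent-to-treat approaches can bias non-inferiority trials toward finding the interventions to be non-inferior", and names the remedy: "we will also conduct a sensitivity analysis including only participants who complete the intervention". It mentions no adjustment for who completes. The EPDS analysis repeats the same procedures on another outcome, so it does not check the choice of analysis set.

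Three other places bear on who completes:
- **Introduction:** "telehealth has the potential to enhance mental health service delivery by reducing access barriers, particularly among minoritized groups". It also reports transportation as a barrier in earlier ROSE research and lists childcare among the barriers to care.
- **Section 3.3.2:** in-person participants get transport, and virtual participants who need a device get a tablet. Both arms are paid per session and can make up missed sessions, including individually by phone or video.
- **Discussion:** virtual delivery is described as a way to increase access, and participants could not choose their modality.

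**The concern.** The completer subset is defined by behaviour after randomisation, so randomisation no longer guarantees that the two groups are comparable. If one modality is easier to attend, its completers are a less selected group than those of the other. If the tendency to complete is also related to how depression scores change, the completer contrast is the modality effect plus a selection term.

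The sign of that term is not known in advance. If people with better expected change complete, and fewer complete in person, the in-person completers look better and the check is too hard on virtual delivery. If people with worse expected change complete, or if in-person completion is the higher one, the check is too lenient. Leniency is the error the analysis was added to guard against. What is at stake is the value of the safeguard as readers will use it to support or doubt the claim.

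**Working it through.** **Inputs from the article.** Target of 900 participants; 20% attrition (10% in pregnancy, a further 10% postpartum); one-sided 5% test; margin d = 0.25.

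**Assumptions, not in the article.** Equal allocation (450 per arm); SD of change of 1, so results are on the d scale; 95% of completers analysed; completion 75% virtual and 55% in person; correlation r between tendency to complete and change of 0.1 to 0.3. Clustering within groups is ignored.

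**The plan's own figure.** No power is stated, so 900 cannot be strictly reproduced. After 20% attrition, 900 × 0.80 = 720 remain, or 360 per arm. The simple formula then gives 95.6% power at a true difference of 0. The sample size is not the problem here.

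**Selection bias.** Suppose each arm keeps the top fraction p of a standard normal tendency to complete. The mean tendency among completers is λ(p) = φ(z_p)/p, where z_p is the normal quantile at p.
- λ(0.75) = 0.424 and λ(0.55) = 0.720, a difference of 0.296.
- Bias = r × 0.296: 0.030 at r = 0.1, 0.059 at r = 0.2, 0.089 at r = 0.3.
- As a share of 0.25: 12%, 24%, 36%.

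**Precision.** Completers analysed: 450 × 0.95 × 0.75 ≈ 321 and 450 × 0.95 × 0.55 ≈ 235. SE = √(1/321 + 1/235) = 0.086.

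**Chance that the completer bound falls below 0.25.** Pass rate = Φ((0.25 − true contrast − bias)/SE − 1.645).

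| r | Bias (SD) | Pass rate, true contrast 0, better-prognosis people complete | Pass rate, true contrast 0.25, opposite selection (false pass) |
|---|---|---|---|
| 0 | 0 | 90% | 5% |
| 0.1 | 0.030 | 82% | 10% |
| 0.2 | 0.059 | 72% | 17% |
| 0.3 | 0.089 | 59% | 27% |

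**Sensitivity to the completion gap, at r = 0.3.** 70% v 60% gives a bias of 0.044 and 13% false passes. 80% v 50% gives 0.134 and 46%.

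**Sensitivity to follow-up.** With 80% of completers analysed, in line with the article's attrition figure, SE = 0.094. At r = 0.3 the pass rate at true equality falls from 85% to 53%, and false passes are 24%. At r = 0.1 the figures are 76% and 9%.

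**When there is no bias.** Equal completion with equal selection cancels exactly. Equal completion alone is not enough: with 70% in both arms, 360 per arm followed up, and selection in one arm only (r = 0.2), the bias is 0.2 × 0.497 = 0.099. Depending on its direction, false passes reach 30%, or the pass rate at true equality drops from 88% to 52%.

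**Does weighting help?** In simulation at 75% v 55%, inverse-probability weighting cut false passes from about 30% to 5% when the baseline predictors captured all of the selection, and to 11% when they captured 70%. In a harsher model it only cut them from about 28% to 20%. The weighted pass rate at a true contrast of 0 was 80%, against 90% for an unbiased completer analysis by the formula.

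**The case against.** **The article does not forecast a completion gap.** A reader might infer that the plan expects modality to change who attends. It does not say so. The Introduction speaks of access to services in general, and section 3.3.2 adds transport, tablets, payment and make-up sessions to even out participation. This stands: differential completion is plausible, not predicted. The supports named do not cover every barrier, however. Childcare, listed in the Introduction, is not among them.

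**The completer result cannot overturn the verdict.** A reader might take the false-pass rates above as error rates of the trial. The decision rule uses the intent-to-treat bound alone, so they are error rates of the sensitivity analysis by itself. This stands in full.

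**The size depends on an unsupported correlation.** This also stands. At r = 0.1 the effect is modest, which is why a range is given.

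**The natural direction is conservative.** If virtual completion is higher and completers do better, the check is too strict rather than too lenient. That is fair, but nothing in the article fixes the direction, and an over-strict check would cast unwarranted doubt on a valid claim.

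**Pairing intent-to-treat with completers is customary, and details may sit in an analysis plan not shown.** Custom supports reporting the comparison. It does not make an unadjusted subset a dependable guard, and the article itself fixes this choice. That it is the only such check can be said of the article, not of any fuller plan.

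**Conclusion.** The concern holds as a weakness of the safeguard. The only check the article names on the intent-to-treat verdict compares groups that randomisation no longer protects, in a trial whose rationale makes arm-dependent completion plausible. It can err either way and so cannot reliably guard against a false non-inferiority claim.

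Under assumed completion of 75% v 55% and correlations of 0.1 to 0.3, the bias uses up between an eighth and just over a third of the margin. Smaller gaps or weaker correlations shrink it; selection that differs by arm creates it even at equal completion. None of these inputs is in the article, so the figures illustrate what could happen and do not predict it. The formal conclusion of the trial is not altered.

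**What to change.** Beside the raw completer comparison, add an adherence-adjusted sensitivity analysis:
- Model completion separately in each arm from baseline data already collected (SCL-20, CESD-10, language, gestational age, sociodemographics).
- Weight completers by the inverse of that probability in the same multilevel model.
- Report completion by arm and label the raw completer result descriptive.
- State in advance how disagreement with intent-to-treat will be read.

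The weighted bound should not become a required second gate; that would be a new decision rule rather than a repair of this one.

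The cost is analysis wording and some programming, with no new data. Recruitment was still open when the article was written, so pre-specification may still be possible. The weighted bound will be somewhat wider, and weighting reduces but does not remove the bias if important predictors of completion are unmeasured.
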